# Quality of Life and Clinical Outcome After Traumatic Spleen Injury (SPLENIQ Study): Protocol for an Observational Retrospective and Prospective Cohort Study

**DOI:** 10.2196/12391

**Published:** 2019-05-06

**Keywords:** quality of life, QOL, spleen, trauma, injury, splenic artery embolization, SAE, embolization, magnetic resonance imaging, observational study

## Abstract

**Background:**

Little is known about the effect of a splenic rupture on the quality of life (QOL) of patients, although the spleen is one of the most frequently injured organs in blunt abdominal trauma. It is essential to obtain more knowledge about QOL after traumatic spleen injury so that this can be taken into account when choosing treatment.

**Objective:**

The primary objective of the SPLENic Injury and Quality of life (SPLENIQ) study is to determine QOL after treatment for traumatic spleen injury. The secondary objective is to investigate clinical and imaging outcome in relation to QOL.

**Methods:**

A combination of a retrospective single-center and a prospective multicenter observational cohort study will be conducted. Patients in the retrospective study have had a splenic injury after blunt abdominal trauma and were admitted for treatment to the ETZ Hospital (Elisabeth-TweeSteden Ziekenhuis) in Tilburg between January 2005 and February 2017. Concerning the prospective cohort study, patients with splenic injury admitted to 1 of the 10 participating hospitals between March 2017 and December 2018 will be asked to participate. The follow-up period will be 1 year regarding QOL, clinical symptoms, and imaging. Patients in the retrospective study will complete 2 questionnaires: World Health Organization QOL assessment instrument-Bref (WHOQOL-Bref) and 12-Item Short-Form Health Survey (SF-12). Patients in the prospective study will complete 5 questionnaires at 1 week, 1 month, 3 months, 6 months, and 12 months after treatment: WHOQOL-Bref, SF-12, Euroqol 5-Dimensional 5-Level (EQ-5D-5L) questionnaire, Institute for Medical Technology Assessment (iMTA) Productivity Cost Questionnaire (iPCQ), and iMTA Medical Consumption Questionnaire (iMCQ). In both the retrospective and prospective study, patients treated with splenic artery embolization will undergo magnetic resonance imaging (MRI). The retrospective group will undergo MRI once, and the prospective group will undergo MRI 1 month and 1 year after treatment. Treatment of splenic injury depends on the severity of the splenic injury, the hemodynamic condition of the patient, and the hospital’s or doctor’s preference. This study is observational in nature without randomization. Concerning the retrospective data, multivariate analysis of covariance will be done. With regard to the prospective data, mixed linear modeling will be performed.

**Results:**

This project was funded in April 2015 by ZonMw. The results of the retrospective study will be expected in March 2019. With regard to the prospective study, inclusion of patients was completed in December 2018 and data collection will be completed in December 2019. The first results will be expected in 2019.

**Conclusions:**

To our knowledge, this is the first study that examines QOL in patients with a traumatic spleen injury. The SPLENIQ study responds to the shortage of information about QOL after treatment for traumatic spleen injury and may result in the development of a patient-oriented protocol.

**Trial Registration:**

ClinicalTrials.gov NCT03099798; https://clinicaltrials.gov/ct2/show/NCT03099798 (Archived by WebCite at http://www.webcitation.org/714ZKV6A0).

**International Registered Report Identifier (IRRID):**

DERR1-10.2196/12391

## Introduction

### Background

Morbidity and mortality are the most commonly used outcome parameters in trauma care literature. However, most patients survive their trauma, and depending on the severity of the trauma, they will be limited in daily life, both physically and mentally. Although quality of life (QOL) is recognized as an important outcome measure, it is still a highly neglected aspect in trauma care studies, including studies with splenic injury patients. Multiple studies that did measure QOL have shown that severely injured patients suffer from psychological complaints and decreased QOL [1-3]. These factors have a major social and economic impact because trauma often involves young patients who frequently are unable to return to work, to reintegrate back into society, or to retrieve their previous activity level [4-11]. In case of splenic injury, treatment choices have to be made in which it is currently unknown what the effects for these patients will be in the short, medium, and long term. When more knowledge becomes available about QOL, it will be useful to determine the choice of treatment.

In blunt abdominal trauma, where the spleen is one of the most frequently injured organs, much is known about morbidity and mortality [12]. Internal bleeding caused by abdominal organ injury is one of the main causes of death after trauma, and a missed splenic rupture is the most common cause of preventable death in trauma patients [13,14]. Presently, the standard of care in hemodynamically stable patients is nonoperative management (NOM), involving close observation of the patient, with success rates up to 90% [12]. A recent study among adults with blunt splenic injury suggests that there are prognostic factors for failure of NOM. Strong evidence exists for prognostic patient factors such as age of 40 years or above, Injury Severity Score of at least 25, and American Association for the Surgery of Trauma splenic injury grade of 3 or higher [15]. Failure of therapy leads to more interventions, longer hospital stay, and higher mortality rates, resulting in increased costs and presumably decreased QOL. When NOM fails, angiography and splenic artery embolization (SAE) can be used as a supplement to NOM. The success rate of SAE ranges between 73% and 100%, with an overall success rate of NOM combined with SAE ranging between 86% and 100% (most studies reporting success rates greater than 90%) [16]. Despite this success rate, much remains unknown about splenic function after SAE, although it is speculated that there is a relationship between splenic volume and the immunologic status of the patient [17-20]. Preservation of splenic function might be one of the biggest advantages of NOM and SAE. However, patients treated with SAE have a risk of developing splenic infarction, abscesses, or cysts, with distal embolization having a significantly higher association with major complications compared with proximal embolization [21,22]. Surgery is indicated when a patient is hemodynamically unstable and does not respond to transfusion or when associated intraabdominal injuries require surgical management. Possible disadvantages of surgery are postsplenectomy complications, such as sepsis, thrombocytosis, and a lifetime risk of invasive infections (overwhelming postsplenectomy infection) [23,24]. All complications may have a major impact on patients’ QOL.

Cost-effectiveness is important in the choice of treatment. Published study results on hemodynamically stable patients with splenic injury favored nonsurgical management over surgery with better clinical and cost results. SAE as a supplement to NOM trended toward being more cost-effective with a shorter hospital stay, despite comparable failure rates. Procedure-related costs were higher for surgery than for SAE, but total hospital costs were not significantly different [25].

### Objectives

There is a growing demand for a (national) guideline or protocol for clinical decision making in traumatic spleen injury. Therefore, it is important to determine the optimal selection criteria for the appropriate management strategy. To achieve this, the entire process surrounding a patient with splenic injury must be considered. Even today, it remains unclear what the impact of QOL is on the entire process. Therefore, the primary objective of this project is to examine the QOL of patients after therapy (NOM, SAE, and surgery) for traumatic spleen injury using a retrospective and prospective group of patients. The secondary objective is to investigate the clinical outcome (eg, complications, reinterventions, and additional therapy), imaging outcome (diagnosis and magnetic resonance spleen imaging after SAE), and cost outcome (cost-effectiveness) and their relation to QOL.

Finally, the data and results acquired from this study may result in the development of a patient-oriented protocol for the management of traumatic spleen injury.

## Methods

### Study Design

A combination of a retrospective single-center and a prospective multicenter observational cohort study will be conducted, assessing the effects of NOM, SAE, and splenectomy in patients with splenic injury after blunt abdominal trauma.

### Participants and Centers of Recruitment

#### Retrospective Study

The study population comprises patients who had a splenic injury after blunt abdominal trauma and were admitted for treatment in the ETZ Hospital (Elisabeth-TweeSteden Ziekenhuis) in Tilburg, the Netherlands, between January 2005 and February 2017. It concerns both men and women who were 18 years or older at the time of screening (February 2017).

#### Prospective Study

The prospective study will be performed in 10 selected Dutch hospitals containing experienced interventional radiologists and trauma surgeons qualified to perform SAE and splenectomy, respectively. The group includes 7 level-1 trauma centers (Erasmus MC, ETZ Hospital, Leiden University Medical Center, Amsterdam University Medical Center, Radboud University Medical Center, Hospital Medisch Spectrum Twente, and Isala Hospital) and 3 level-2 trauma centers (Maasstad Hospital Rotterdam, Albert Schweitzer Hospital Dordrecht, and Amphia Hospital Breda). The study will be organized in a network infrastructure in which radiologists and trauma surgeons collaborate.

All patients with a splenic injury after abdominal trauma confirmed by ultrasound/focused assessment with sonography in trauma (US/FAST) and/or computed tomography (CT) at the primary trauma screening at the 10 participating hospitals between March 2017 and December 2018 will be asked to participate.

### Inclusion and Exclusion Criteria

#### Retrospective Study

The inclusion criteria are patients (1) diagnosed with splenic injury after trauma; (2) who underwent NOM, SAE, or surgery at the ETZ Hospital; (3) diagnosed between January 2005 and February 2017; and (4) who were aged 18 years or older at the time of screening (February 2017). Patients will be excluded from questionnaires in case of (1) insufficient knowledge of the Dutch language (verbal and writing) or (2) obviously, death. Patients treated with SAE will be excluded for magnetic resonance imaging (MRI) when they do not want to or are not able to undergo an MRI abdomen (eg, pregnancy or other contraindications).

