#### Prospective Study

To be eligible to participate, patients (1) must be aged 18 years or older, (2) have splenic injury after abdominal trauma (confirmed by US/FAST and/or CT), and (3) must be treated in 1 of the 10 participating hospitals between March 2017 and December 2018. Exclusion criteria are identical to those of the retrospective study.

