#### Questionnaires

Patients in the retrospective study will complete the questionnaires once. Patients in the prospective study will complete questionnaires at 1 week and 1, 3, 6, and 12 months after treatment (see Table 3).

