### Statistical Analysis

All analyses will be conducted using SPSS V24.0 (Statistical Package for Social Sciences, Chicago Illinois, USA). Frequencies and descriptive statistics will be calculated to provide an overview of the characteristics of the study population. Statistical test results will be considered significant at a level of *P*<.05.

Concerning the retrospective study, a MANCOVA will be done after correcting theoretically important covariates to assess the differences between treatment groups on the 4 WHOQOL-Bref domains and the general facet. For each type of treatment, a 1 sample *t* test will be performed for each WHOQOL-Bref scale to compare the QOL scores with reference data.

For both the retrospective and prospective studies, a logistic regression analysis will be performed on the outcome variables’ (1) need for reintervention (yes/no) and (2) for each complication (yes/no), assessing the effect of treatment after correcting for theoretically important covariates. With regard to hospital stay in days, a Kruskal-Wallis test will be performed with the group (type of treatment) and days in hospital. Analysis of covariance will be used to compare proximal versus distal SAE, thereby correcting the effect for theoretically important covariates. To confirm/find prognostic factors for failure of NOM, a logistic regression analysis will be performed if NOM is a failure quickly after treatment. Otherwise, a survival analysis will be performed.

Regarding the prospective study, to assess the differences between groups in their change in QOL over time, a linear mixed model analysis will be conducted. To answer our research question, we will focus on the interaction effect between measurement occasion and treatment group, while correcting for theoretically important covariates. For the repeated measures, an unstructured covariance matrix will be used. Item-level missing values will be imputed according to the guidelines of the questionnaires. Scale-level missing values will be handled directly through maximum likelihood estimation, because the mixed model procedure makes use of all available data for each participant over all time points.

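### The retrospective age limit is set at screening in February 2017, so some patients injured as minors enter the record-based models, depending only on calendar date

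*Protocol article*

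**What the plan says.** The protocol article states the retrospective age rule twice, in the same sense. The retrospective part of Participants and Centers of Recruitment says: "It concerns both men and women who were 18 years or older at the time of screening (February 2017"). The retrospective list under Inclusion and Exclusion Criteria repeats it: "who were aged 18 years or older at the time of screening (February 2017"). The injury window in that list is "diagnosed between January 2005 and February 2017".

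The exclusions that follow concern language and death, and they apply to the questionnaires only: "Patients will be excluded from questionnaires in case of (1) insufficient knowledge of the Dutch language (verbal and writing) or (2) obviously, death". A further exclusion concerns MRI. None refers to age at injury, so the age rule governs the whole retrospective cohort, including the analyses that need only the patient record.

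Prospective patients "must be aged 18 years or older" and are identified on admission, so they are adults at injury.

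Quality of life (QOL) is measured at one time point in the retrospective cohort: "Patients in the retrospective study will complete the questionnaires once". Under Statistical Analysis, "a MANCOVA will be done after correcting theoretically important covariates to assess the differences between treatment groups" on the WHOQOL-Bref scales. Logistic models for reintervention and for each complication are planned in both cohorts. An analysis of prognostic factors for NOM failure is also planned. The Background gives the source of those factors: "A recent study among adults with blunt splenic injury suggests that there are prognostic factors for failure of NOM".

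**The concern.** Testing age at one fixed calendar date, for injuries spread over some 12 years, yields neither an adult cohort nor an all-ages one. A child injured at 10 in 2006 had turned 18 by February 2017 and is in. A child injured at 10 in 2012 had not and is out. Nothing about the injury, the treatment or the outcome separates the two.

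This has two consequences. Age at injury and time since injury become linked by the rule itself, in a cohort whose QOL is measured once at whatever interval has elapsed. And the models of NOM failure, reintervention and complications take in an arbitrary slice of pediatric injuries. Age at injury is itself a candidate predictor of NOM failure: the Background lists age 40 or above, from a study in adults. The same reintervention and complication models are to be fitted in a prospective cohort with no minors, so the two sets of estimates would refer to different populations.

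**Working it through.** **Inputs from the article.** Injury window January 2005 to February 2017; age 18 or older in February 2017; retrospective sample size 138 at f² = 0.061, power 0.80 and significance level .05; 135 for a medium effect.

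**The plan's own figure.** The MANCOVA sample size can be reproduced with 3 treatment groups and 5 responses (four domains and the general facet), using Pillai's trace:
- df1 = 5 × 2 = 10; df2 = 2(N − 6); noncentrality λ = 2 × N × f².
- N = 138, f² = 0.061: df2 = 264, λ = 16.84, power 0.801.
- f² = 0.0625 (assumed here for the medium effect): the smallest N with power 0.80 is 135.

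Both stated figures are confirmed. The age rule does not affect them; they are used below to price a restriction.

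**Youngest eligible age at injury.** The window is 12.0 to 12.2 years, depending on the days chosen within the two months. 18 − 12.2 = 5.8 and 18 − 12.0 = 6.0, so about age 6.

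**Link between age at injury and time since injury.** A patient injured at age a < 18 needs at least 18 − a years since injury. With a window of 12.16 years, the share of the window in which that patient is eligible is (12.16 − (18 − a)) / 12.16.

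| Age at injury | Minimum years since injury | Share of window eligible |
|---|---|---|
| 6 | 12 | 1% |
| 8 | 10 | 18% |
| 10 | 8 | 34% |
| 12 | 6 | 51% |
| 14 | 4 | 67% |
| 16 | 2 | 84% |
| 17 | 1 | 92% |
| 18 or older | 0 | 100% |

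If injuries are spread evenly over the window, mean time since injury is 12.16 / 2 = 6.1 years for adults. For an eligible minor it is (18 − a + 12.16) / 2: 9.1 years if injured at 12 and 11.1 years if injured at 8, but only 6.6 years if injured at 17.

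**How many minors.** The article gives no count, so this is a range under stated assumptions: injuries spread evenly over T = 12.08 years, adults injured at ages 18 to 70 (52 years of age), and each year of age below 18 contributing r times as many patients as an adult year. For an injury t years before screening, t years of age below 18 are eligible, so the share of minors is r·t / (52 + r·t). Averaged over t from 0 to T:

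share = 1 − (52 / (r·T)) × ln(1 + r·T / 52)

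| r | Share of minors | Out of 138 |
|---|---|---|
| 0.25 | 2.8% | 4 |
| 0.5 | 5.4% | 7 |
| 1 | 10.1% | 14 |
| 2 | 17.9% | 25 |

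**Price of restricting the MANCOVA.** If exactly 138 were enrolled and the minors removed, with f² = 0.061:
- r = 1: N = 138 − 14 = 124, df2 = 236, λ = 15.13, power 0.744.
- r = 2: N = 138 − 25 = 113, df2 = 214, λ = 13.79, power 0.692.

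**The case against.** The rule is consistent in both places and looks deliberate. Retrospective patients receive a letter, sign their own consent and answer once, so requiring adulthood when they answer fits the outcome. The one-sample t tests compare current QOL with reference data, for which age when answering is the relevant age. The objective speaks of patients after therapy and never says that the retrospective cohort must be adult at injury. All of this stands, and it is why the questionnaire analyses should keep their population.

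Age is collected, covariate correction is planned, and the Discussion adds propensity scores. Naming the covariates can be left to a fuller document. This also stands, so the absence of a covariate list is not the point here. But adjustment does not explain why eligibility for a record-based model should turn on the calendar date.

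A reader might infer more than the documents support:
- That patients injured as minors are always those longest since injury. They are not: someone injured at 16 or 17 qualifies after 1 to 2 years, and adults also span the whole window.
- That minors cluster in one treatment group and so bias the MANCOVA contrast. The article attributes treatment choice to injury severity, hemodynamic condition and hospital or doctor preference. It says nothing about how minors were treated.
- That the retrospective results cannot be set beside the prospective ones. No pooled or cross-cohort test is planned. The populations differ in age at injury, which limits direct comparison but does not rule it out.

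**Conclusion.** The point holds for the record-based models. The rule admits patients injured from about age 6 on a condition that depends only on calendar date, links age at injury to time since injury, and departs from the adult-at-injury prospective cohort. For NOM failure, reintervention and complications the article offers no reason for it, and the NOM-failure factors it cites come from adults.

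The eligibility arithmetic is firm. The share of minors is not: 3% to 18% rests on evenly spread injuries, an adult age range of 18 to 70 and relative rates of 0.25 to 2, none of which is in the article. No bias in WHOQOL-Bref points or odds ratios can be computed, and its direction is unknown. For the MANCOVA and the t tests the age limit is defensible; there the link with time since injury calls for adjustment and a sensitivity analysis, not for a different primary population.

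**What to change.** 1. Run the retrospective models of NOM failure, reintervention and complications in patients aged 18 or older at injury, matching the prospective criterion. Give the all-ages result as a sensitivity analysis.
2. Keep the MANCOVA in all eligible patients, and adjust for age at injury and time since injury. Together these two also fix age at the questionnaire. Add a sensitivity analysis in those aged 18 or older at injury.
3. Report how many patients were injured as minors, by treatment group, so that the reader can judge the matter directly.

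Age is already collected, and age at injury and time since injury should be derivable from dates in the patient records, so no new data collection is needed. The cost is somewhat fewer patients in the record-based models and a little more analysis. The Results section says the retrospective database is complete, so the change should be declared as specified after data collection. Making the restriction primary for the MANCOVA is not advised: at 138 enrolled, power would fall from 0.80 to about 0.74 (N = 124) or 0.69 (N = 113).

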#### Prospective Study

To be eligible to participate, patients (1) must be aged 18 years or older, (2) have splenic injury after abdominal trauma (confirmed by US/FAST and/or CT), and (3) must be treated in 1 of the 10 participating hospitals between March 2017 and December 2018. Exclusion criteria are identical to those of the retrospective study.

### Sample Size Calculation

As the World Health Organization QOL assessment instrument-Bref (WHOQOL-Bref) comprises multiple facets, the *retrospective data* will be analyzed using a multivariate analysis of covariance (MANCOVA). This technique is more powerful than a univariate analysis of variance, resulting in a required sample size of 135 patients giving a medium effect and power of 0.80. Previous research [26] indicates that the minimal clinically important difference (MCID) of the WHOQOL-Bref slightly varies across its domains. Table 1 shows for each domain the MCID and standard deviation. On the basis of these statistics, the Cohen *d* effect sizes were calculated and transformed via Cohen *f* to the *f*^2^ effect sizes required in the MANCOVA power analysis. It turns out that 138 participants are required to detect the average *f*^2^ of 0.061 with a power of 0.80, given a significance level of .05.

With regard to the *prospective data*, mixed linear modeling will be used. Power analysis is performed for a repeated measures design investigating the interaction between treatment and time. We assumed a significance level of .05 and a medium effect size of partial eta squared of 0.05 and an average correlation of 0.50 among the 5 repeated measurements. On the basis of this, we require 33 participants to test with a power of 0.80, whether the 3 treatment groups differ in their change in QOL over the follow-up time. When assuming an effect size similar to the MCID’s reported in the table above, 27 participants are required to detect the medium effect of *f*=0.248 with a power of 0.80.

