### Study Procedures

#### Retrospective Study

The clinical and imaging data of all splenic injury patients will be collected from the electronic patient files and registered anonymously. To measure QOL, all patients who are still alive will receive a written letter explaining the study, an informed consent form, the questionnaires, and a prestamped return envelope by mail. When a patient is willing to participate, he/she will sign the consent form and send it back in the return envelope, together with the completed questionnaires, assessing QOL and health status. When patients do not complete or return the questionnaires within 2 weeks, they receive a phone call as a reminder. When patients do not want to participate, the reason will be noted if the patient wants to let it be known. The patients who underwent SAE will be called for a voluntary single MRI abdomen at the ETZ Hospital in Tilburg.

This study has been reviewed and approved by the Medical Ethical Committee Brabant (METC Brabant, protocol number: NL54339.028.15) on January 27, 2016. The study has also been approved by the local ethical committee of the ETZ Hospital on February 9, 2016.

**Table 1 table1:** Minimal clinically important difference (MCID) per WHOQOL-Bref domain.

Domain	MCID	SD	Cohen *d*	Cohen *f*	Effect size *f*^2^
Physical	1.545	3.1	0.498	0.249	0.062
Psychological	1.259	2.5	0.504	0.252	0.063
Social	1.274	2.6	0.490	0.245	0.060
Environmental	1.142	2.3	0.497	0.248	0.062
General	0.876	1.8	0.487	0.243	0.059
Average	1.219	2.460	0.495	0.248	0.061

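### The retrospective sample size of 138 enters an averaged single-domain f-squared as a multivariate effect, so the stated power of 0.80 for MCID-sized differences does not follow from Table 1

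*Protocol article*

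**What the plan says.** The Sample Size Calculation section of the protocol article gives two figures for the retrospective cohort. The first rests on a conventional medium effect: "This technique is more powerful than a univariate analysis of variance, resulting in a required sample size of 135 patients". The second rests on Table 1, which lists MCID, SD, d, f and f-squared for each of the four WHOQOL-Bref domains and the general facet. The section says that d was converted through f to the f-squared "effect sizes required in the MANCOVA power analysis", and concludes: "It turns out that 138 participants are required to detect the average" f-squared of 0.061 "with a power of 0.80, given a significance level of .05". The last row of Table 1 reads "Average 1.219 2.460 0.495 0.248 0.061".

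The retrospective inclusion criteria define three treatment groups: patients "who underwent NOM, SAE, or surgery at the ETZ Hospital". The Statistical Analysis section compares these groups on five scales. The article's calculation uses no mean pattern across the three groups, no treatment split and no correlation between scales.

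**The concern.** Each f in Table 1 is d/2, the conversion for two equal groups, and each f-squared describes one outcome. The planned test compares three groups on five correlated outcomes. Its effect size is a function of the Pillai trace and cannot be obtained by averaging single-outcome values. If the average was used as the multivariate effect, the link from an MCID-sized difference to power 0.80 is broken.

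The retrospective MANCOVA serves the primary objective, and the Discussion says the sample size was set for that objective. Because 138 is tied explicitly to the MCID, a reader could take a non-significant global test as good evidence against MCID-sized treatment differences. That reading needs the power to be what is stated.

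**Working it through.** **Inputs from the article.** Alpha 0.05, power 0.80, k = 3 groups, p = 5 outcomes, average d = 0.495, f = 0.248, f-squared = 0.061 (Table 1).

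**1. Reproduce the stated figures.** Global Pillai test: s = min(p, k − 1) = 2, df1 = p(k − 1) = 10, df2 = s(N − k − p + s) = 2(N − 6), noncentrality = s × N × f2(V), noncentral F.
- f2(V) = 0.0625 (f = 0.25): N = 135, power 0.8016.
- f2(V) = 0.061: N = 138, power 0.8008; noncentrality 2 × 138 × 0.061 = 16.8.
- Up to five covariates leave 138 unchanged.
- Variants that do not give 138: four outcomes (128), six outcomes (148), two groups with five outcomes (216), univariate three-group ANOVA (160 at f = 0.248, 161 at f-squared 0.061).

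The step from 0.061 to 138 is therefore correct arithmetic. The problem is the effect size that was entered.

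**2. The conversion f = d/2.** For three equal groups with a largest gap of d:
- third group midway: f = d × sqrt(1/6) = 0.408 × 0.495 = 0.202, f-squared 0.041;
- two groups together, one apart: f = d × sqrt(2/9) = 0.471 × 0.495 = 0.233, f-squared 0.054.

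Even if these were still entered as f2(V), N would be 204 and 154, and power at 138 would be 0.59 and 0.74.

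With unequal groups f can reach d/2. With a 50/25/25 split and the half-sized group differing, f = d × sqrt(0.5 × 0.5) = 0.5d. With an assumed 80/35/23 split and the group of 80 differing, f = d × sqrt(80 × 58)/138 = 0.494d.

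**3. From single-domain differences to f2(V).** Assume a common correlation r between scales, and let c = 1/6 or 2/9 for the two equal-group patterns. If all five scales shift by d, the single non-zero root is c × d² × 5/(1 + 4r), V = root/(1 + root), and f2(V) = V/(2 − V). Example with r = 0.5 and c = 2/9: root = 0.0545 × 5/3 = 0.0908, V = 0.083, f2(V) = 0.043. With c = 1/6 it is 0.033. Neither is 0.061.

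If only one scale shifts, the factor 5/(1 + 4r) becomes (1 + 3r)/((1 − r)(1 + 4r)).

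Power at N = 138 with equal groups (lower value: third group midway; upper value: one group apart), with the N needed for 0.80 in brackets:

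| Assumed r | All five scales shifted | One scale shifted |
|---|---|---|
| 0 | 0.95 to 0.99 (93 to 73) | 0.29 to 0.38 (411 to 312) |
| 0.3 | 0.63 to 0.78 (188 to 144) | 0.35 to 0.47 (336 to 255) |
| 0.5 | 0.48 to 0.62 (251 to 192) | 0.48 to 0.62 (252 to 192) |
| 0.7 | 0.38 to 0.50 (315 to 239) | 0.73 to 0.86 (160 to 123) |

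Simulation with 5,000 runs in four of these settings agreed within about 1.5 percentage points (for example 0.39 against 0.38 for one scale, r = 0, one group apart).

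**4. Unequal groups.** With the assumed 80/35/23 split, all five scales shifted and a single group differing, power over r = 0.3 to 0.7 is 0.82 to 0.55 if the largest group differs, 0.70 to 0.43 if the middle one does, and 0.54 to 0.31 if the smallest does. The overall range is about 0.31 to 0.82.

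**5. The comparison with univariate analysis.** With the same f-squared, the univariate noncentrality is N × f-squared = 138 × 0.061 = 8.4, half of 16.8. The fall from about 160 to 138 comes from reusing one f-squared with the doubled noncentrality, partly offset by 10 rather than 2 numerator degrees of freedom. With f for three equal groups, univariate ANOVA needs 180 to 239. The multivariate test with all five scales shifted needs 73 to 93 at r = 0 but 192 to 251 at r = 0.5.

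**The case against.** Several points on the other side stand.

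- It is tempting to call f = d/2 simply invalid for three groups. The documents do not support that. Allocation is observational, equal groups are nowhere assumed, and step 2 shows splits that give d/2 or nearly so. If one MCID separated each adjacent pair of equal groups, f would be 0.404 and power at 138 at least 0.89. The fair charge is that the conversion fits only particular patterns and splits, and the article states none.
- A reader might infer that the study is underpowered. That does not follow either: with weakly correlated scales all shifted, power exceeds 0.80, and covariate adjustment could raise it further, although no R-squared is given.
- A reader might also infer that the claimed advantage of MANCOVA is false. It is real under some inputs and absent under others, so it needs qualifying, not deleting.
- The number 138 did not act as a recruitment stop. Under Study Procedures every surviving patient is approached, and the Results section says the retrospective database is complete. The per-treatment comparisons with reference data do not depend on this calculation.

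None of this supplies the missing link. Even in the 50/25/25 case where f equals d/2 exactly, power with all five scales shifted is 0.83 at r = 0.3 and 0.68 at r = 0.5.

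**Conclusion.** The point holds in this form: 135 and 138 come from entering a single-domain f-squared as the Pillai f2(V), and the stated power of 0.80 for MCID-sized differences cannot be derived from Table 1. Over the equal-group settings examined, power at 138 runs from about 0.29 to 0.99; with all five scales shifted it is 0.48 to 0.62 at correlation 0.5. These values rest on an assumed common correlation, on the mean patterns shown and on no gain from covariates. The 80/35/23 split is illustrative and has no source in the article. The two printed sample sizes do not contradict each other, since they belong to two slightly different effect sizes. What is affected is the stated power and the weight a null global test can carry, not enrolment or the choice of test.

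**What to change.** Replace the statement of 135 and 138 at power 0.80 with power at the achieved retrospective N. Derive it from a stated three-group mean pattern expressed in MCIDs, the achieved treatment split, and either the observed correlations between the WHOQOL-Bref scales or a stated range of them. Compute Pillai V from these inputs and report power as a range. Reword the sentence on MANCOVA being more powerful than univariate analysis so that it is conditional on the same inputs.

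The cost is a recalculation and a few sentences. No patients are added and the analysis does not change. The single figure of 0.80 becomes a range that may be less favourable.
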